## Abstract

**Objective:**

Incomplete recovery from facial palsy has a long-term impact on the quality of life, and medical options for the sequelae of Bell's palsy are limited. Invasive treatments and physiotherapy have been employed to relieve symptoms, but there is limited clinical evidence for their effectiveness. Acupuncture is widely used on Bell's palsy patients in East Asia, but there is insufficient evidence for its effectiveness on Bell's palsy sequelae. The objective is to evaluate the efficacy and safety of acupuncture in patients with sequelae of Bell's palsy.

**Method/Design:**

This study consists of a randomized controlled trial with two parallel arms: an acupuncture group and a waitlist group. The acupuncture group will receive acupuncture treatment three times per week for a total of 24 sessions over 8 weeks. Participants in the waitlist group will not receive any acupuncture treatments during this 8 week period, but they will participate in the evaluations of symptoms at the start of the study, at 5 weeks and at 8 weeks after randomization, at which point the same treatment as the acupuncture group will be provided. The primary outcome will be analyzed by the change in the Facial Disability Index (FDI) from baseline to week eight. The secondary outcome measures will include FDI from baseline to week five, House-Brackmann Grade, lip mobility, and stiffness scales.

**Trial registration:**

Current Controlled-Trials ISRCTN43104115; registration date: 06 July 2010; the date of the first patient's randomization: 04 August 2010

## Background

Bell's palsy is an acute, idiopathic, unilateral paralysis of the face. Its cause is unknown, but mounting evidence suggests that reactivated herpes viruses from cranial nerve ganglia play a key role in the development of this condition; its pattern is consistent with that of peripheral neural dysfunction [1,2]. Inflammation of the facial nerve initially results in reversible neuropraxia and Wallerian degeneration ultimately ensues [1].

The incidence of Bell's palsy is approximately 30/100,000 people per year [3]. The prognosis is good, and approximately 70% of patients recover completely within 6 months without treatment. However, 30% of Bell's palsy patients have sequelae, such as residual paresis (29%), contracture (17%), and facial spasm or synkinesis (16%) [3]. The incomplete recovery of facial symmetry can have a long-term impact on the quality of life, such as difficulty with drinking, eating and speaking, as well as psychosocial problems [4]. The symmetry of the face is a determinant of facial charm and influences interpersonal attraction [5].

Medical options for the sequelae of Bell's palsy are limited to invasive treatments, such as injection of Botulinum toxin A and surgical reconstruction. Patients may be referred to physiotherapists as well, although there is no evidence favoring one intervention over another [5-8]. According to a 2009 study, the effect of steroids on acute Bell's palsy within 72 hours of the onset of symptoms is clinically effective, but steroids are not used on the sequelae of Bell's palsy [9,10].

Acupuncture is known to be a safe treatment and is used for a wide range of symptoms associated with Bell's palsy [11]. In a 2007 systematic review, the effect of acupuncture on Bell's palsy was inconclusive [12]. This stems from limited clinical studies on acupuncture for Bell's palsy and various errors in the design of some of those studies. To overcome such problems, a large-scale clinical trial investigating the effect of acupuncture on Bell's palsy is under way [13]. Here, our aim is to evaluate the safety and efficacy of acupuncture on the sequelae of Bell's palsy.

## Method/Design

### Objective

The primary objective of this study is to investigate the efficacy and safety of acupuncture in patients with sequelae of Bell's palsy.

### Primary outcome

The change in the Facial Disability Index (FDI) social [14] score after completing eight weeks of acupuncture treatment will be compared to the score prior to treatment. This scoring system consists of two domains; physical score and social score, and has been investigated for the reliability and validity [14]. FDI-social score evaluations will be performed on the first visit, the fifth- and eighth-week visits. Participants will answer five multiple choice questions related to problems associated with facial muscle function during the previous month.

### Secondary outcome

Secondary outcome measures will include FDI-social score from baseline to week five, FDI-physical score, House-Brackmann (H-B) Grade [15], lip mobility (lip-length and snout indices) [16], and stiffness scales [17]. The H-B grade has been tested for its reliability [18] and lip-length and snout indices showed a high correlation with H-B Grade [19]. Stiffness scale is a simple five-point scale for facial stiffness (1 = no stiffness, 5 = very stiff) [17].

Unfortunately, there has been no validation study of Korean version of each of the primary and secondary outcomes. In our study, two professional translators made each outcome measurement questionnaire in Korean, which has been used in our clinical facial palsy center for evaluating sequelae of facial palsy. So we decided that these questionnaires are readable and suitable to our study.

### Design

A randomized, assessor-blinded, waitlist controlled trial will be conducted at the Acupuncture and Moxibustion Department of Kyung Hee University's Oriental Medical Hospital in Seoul. (Figure 1) The study includes a screening period before randomization and a treatment period of 8 weeks (3 sessions per week). After screening for inclusion/exclusion criteria, subjects will be randomized to either the acupuncture group or the waitlist group, in accordance with a computer-generated random number list that is hidden until the start of treatment. No-acupuncture waitlist control is used as a control because sham acupuncture cannot be substituted for a physiologically inert placebo [20].

**Figure 1 F1:**
[figure not shown]
**Chronological Flow Chart of the Study Design**.

### Eligibility

#### Inclusion criteria

To be included, patients have to be diagnosed with Bell's palsy at least six months prior to screening. Patients must score less than 70 on the physical aspect of the FDI, less than 80 on the social aspect and provide written informed consent. Participants who are 18 to 65 years old will be recruited using local newspaper advertisements and posted notices.

#### Exclusion criteria

Participants will be excluded if they suffer from serious medical conditions, such as uncontrolled hypertension, diabetes mellitus requiring insulin injection, past or current malignant tumors, severe dyslipidemia, liver or kidney dysfunction, anemia, active pulmonary tuberculosis or other infectious or systemic diseases that are inappropriate for treatment with acupuncture.

Eligible participants will be excluded if they have complicated pathophysiologic conditions of secondary facial palsy from infection, multiple neuritis, tumors invading the temporal bone, brain contusion or stroke. Patients with Ramsay-Hunt Syndrome [21] will also be excluded from the study, as well as those with bilateral or recurrent facial palsy. To avoid confounding effects that can influence patients' outcome measures, the oral administration of steroids or antiviral drugs (acyclovir, valaciclovir, famciclovir, or ganciclovir), a surgical history for facial palsy, such as facial nerve decompression, reconstruction of the facial nerve or muscle, and history of acupuncture, moxibustion, vesiculation and massage therapy within three months will also result in exclusion from the study. With regard to safety and compliance issues, patients with other neurological illnesses, neuropsychiatric diseases, present or planned pregnancy, current lactation, or scars on the treatment area will also be excluded.

Over-the-counter (OTC) drugs for common colds, dyspepsia, headaches, etc. will be allowed. However OTC drugs of unknown components or indicated for Bell's palsy related symptoms will not be allowed. All patients will be instructed to disclose all medication use prior to enrollment. Records on the drugs taken by each patient will be obtained at every visit, and patients will be requested to inform us of any change to their medication or supplement regimen. Additional acupuncture treatments, herbal medicines, or medical interventions elsewhere will not be allowed throughout the study.

### Acupuncture treatment protocol

#### Acupuncture intervention

Acupuncture will be performed by specialists in oriental medicine. Participants will be randomly assigned to the acupuncture treatment group or the waitlist group. The acupuncture group will receive acupuncture treatments 3 times/week for a total of 24 sessions over 8 weeks, following the details of the STandards for Reporting Interventions in Clinical Trials of Acupuncture (STRICTA) 2010 checklist as shown in Table 1. In the acupuncture treatment group, 18 acupuncture points [22] (ST4, ST6 on the unaffected side, ST1, EX-HN4, TE23, LI20 on the affected side, TE17, ST9, LI10, LI4, ST36 and GB34 on both sides) will be used. These selected acupuncture points were based on acupuncture specialist forums and the textbook of acupuncture in Korea [23].

**Table 1 T1:** Details of the proposed acupuncture intervention according to the STRICTA 2010 Checklist

Acupuncture rationale	Style of acupuncture	Traditional Korean Medicine
	
	Rationale for treatment	Acupuncture has been historically used to treat facial palsy. Additionally, it is known to be a safe treatment used in a wide range of symptoms caused by Bell's palsy [11].
	
	Extent to which treatment varied	The subjects of the acupuncture group all receive the same treatment
**Details of needling**	Number of needle insertions per subject per session	18
	
	Names of the insertion points (uni/bilateral)	ST4, ST6, (unilateral, unaffected side) ST1, EX-HN4, TE23, LI20 (unilateral, affected side) TE17, ST9, LI10, LI4, ST36 and GB34 (bilateral)
	
	Depth of insertion	5-30 mm (exact depth shown in Table 2)
	
	Response sought	De-qi
	
	Needle stimulation	Manual
	
	Needle retention time	10 minutes
	
	Needle type	0.20 mm (diameter) × 30 mm (length) disposal needle (Dongbang Acupuncture Inc, Boryeong, Korea)

**Treatment regimen**	Number of treatment sessions	24
	
	Frequency and duration of treatment sessions	3 sessions/week for 8 weeks

**Other components of treatment**	Details of other interventions administered to the acupuncture group	No other interventions are done
	
	Setting and context of treatment	All subjects are informed that they will receive acupuncture treatment, which can potentially reduce the sequelae of Bell's palsy symptoms; however, the control group would have to complete the three evaluations during the first 8 weeks before receiving the same treatment as the acupuncture group.

**Practitioner background**	Description of participating acupuncturists	Specialists in Oriental Medicine with at least 3 years of practice in acupuncture

**Control or comparator interventions**	Rationale for the control or comparator in the context of the research question	No-acupuncture waitlist control is used as a control because sham acupuncture cannot be a substituted for a physiologically inert placebo [20]
	
	Precise description of the control or comparator	The control group forms a waitlist and completes the evaluations during the first 8 weeks after randomization before receiving the same treatment as the acupuncture group.

A 0.20-mm (diameter) × 30-mm (length) disposal needle (Dongbang Acupuncture Inc, Boryeong, Korea) (Table 1) will be inserted into each acupuncture point to a depth of 5-30 mm, depending on the points selected. All participating acupuncture doctors will use de-qi sensation techniques to manually manipulate and maintain the needles for a 10-minute period with manipulation at the start and end of the 10-minute period. Additional interventions, i.e., infrared irradiation or electronic stimulation, will not be allowed during the acupuncture treatment. The ST4 and ST6 needles will penetrate to a depth of 20 to 30 mm using an oblique angle of insertion toward each other's tips. The ST1 and EX-HN4 needles will penetrate to a depth of 5 to 10 mm at an oblique angle toward the eye, using caution so as not to damage the conjunctiva when applying the ST1 needle. The TE23 needle will penetrate to a depth of 20 to 30 mm at an oblique angle toward the ear. The LI20 needle will be inserted to a depth of 20 to 30 mm at an oblique angle toward the root of the nose. The TE17, ST9, LI10, LI4, ST36 and GB34, needles will be inserted perpendicular to the skin to a depth of 20 to 30 mm. (Table 2) These manipulations will be repeated after 10 minutes. Needling will be carried out with participants in the supine position, and needle sites will be swabbed with 2% boric acid before insertion. Upon withdrawal of the needle, dry sterilized cotton balls will be firmly applied to the insertion points.

**Table 2 T2:** Acupuncture Points and Needling Procedure

Acupuncture Point	Direction	Depth (mm)
ST4 (unaffected side)	Transversely, toward ST6	20-30

ST6 (unaffected side)	Transversely, toward ST4	20-30

ST1 (affected side)	Transversely, toward the eye	5-10

EX-HN4 (affected side)	Transversely, toward the eye	5-10

TE23 (affected side)	Transversely, toward the ear	20-30

LI20 (affected side)	Obliquely along nasolabial sulcus toward the root of nose	20-30

TE17 (both sides)	Perpendicular to the skin	20-30

ST9 (both sides)	Perpendicular to the skin	20-30

LI10 (both sides)	Perpendicular to the skin	20-30

LI4 (both sides)	Perpendicular to the skin	20-30

ST36 (both sides)	Perpendicular to the skin	20-30

GB34 (both sides)	Perpendicular to the skin	20-30

### Outcome measures

After screening, the participants will answer the FDI questionnaire three more times: at the first visit, at five weeks, and at eight weeks after the final treatment. The assessment of H-B Grade, lip mobility, and stiffness will be conducted at each time point.

The expectations of the participants will be recorded using the credibility and expectancy questionnaire [24] to determine whether expectations affected outcomes.

Any adverse events as a result of acupuncture will be monitored and recorded. At the end of the trial, the participants in the acupuncture group will be asked if they are satisfied with the outcome.

Because the knowledge of the group assignment could modify outcome assessment, we will ensure that the independent assessor is blinded.

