### Statistical methods

#### Analysis

Analysis will be performed for an intention-to-treat population consisting of all randomized participants regardless of their actual treatment received. Any missing data will be replaced with ones by a multiple imputation technique [25]. All data will be analyzed descriptively. Of the primary and secondary outcome measurements, variables of FDI, H-B grade and stiffness scale are discrete ordinal variables whereas lip mobility is recorded as a continuous variable. For primary and secondary outcome measurements, the mean differences from the baseline values to the end of treatment will be compared between the two groups using the two-sample t-test if the data are distributed normally. In case of non-normally distributed data, Wilcoxon rank-sum test will be performed. If baseline values of outcome measurements are significantly different between groups, analysis of co-variance (ANCOVA) will be performed using any imbalanced variables as covariates and assigned group as fixed factor.

All adverse events reported during the study will be included in the clinical report, and the prevalence of adverse events will then be calculated. The percentage of subjects with adverse events in each group will be calculated and compared using the chi-squared test or Fisher's exact test.

Statistical analyses will be performed using the SAS statistical package program (ver. 9.1.3), and the level of significance will be established at α = 0.05.

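### The Outcome measures section places the last assessment eight weeks after the final treatment, which contradicts the week-8 endpoint stated elsewhere and, if followed literally, leaves no week-8 measurement

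*Protocol article*

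**What the plan says.** The protocol article dates the last assessment in several places.

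- **Outcome measures:** after screening, the FDI is completed three more times, "at the first visit, at five weeks, and at eight weeks after the final treatment". The next sentence ties House-Brackmann grade, lip mobility and stiffness to the same time points.
- **Abstract, Method/Design:** "The primary outcome will be analyzed by the change in the Facial Disability Index (FDI) from baseline to week eight". Waitlist participants are evaluated at the start and "at 5 weeks and at 8 weeks after randomization, at which point the same treatment as the acupuncture group will be provided".
- **Primary outcome:** "FDI-social score evaluations will be performed on the first visit, the fifth- and eighth-week visits". The same section describes the endpoint as the "score after completing eight weeks of acupuncture treatment will be compared to the score prior to treatment".
- **Acupuncture intervention and Table 1:** treatment is given "3 times/week for a total of 24 sessions over 8 weeks", and "the control group would have to complete the three evaluations during the first 8 weeks before receiving the same treatment as the acupuncture group". The comparator row of Table 1 repeats this and counts the 8 weeks from randomisation.
- **Analysis:** "the mean differences from the baseline values to the end of treatment will be compared between the two groups".
- **Randomization and allocation:** waitlist participants wait 8 weeks and then have acupuncture over a further 8 weeks.

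**The concern.** The time of the primary endpoint is stated in two ways that cannot both be followed. In a waitlist design this matters more than usual, because week 8 is the last point at which an untreated comparator exists. After that, the control arm is offered the same course.

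The late assessment cannot be read as an additional follow-up visit. Outcome measures counts exactly three assessments after screening, so the late one takes the place of week 8. Because the secondary measures are tied to the same time points, their week-8 assessment would go as well.

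A related looseness sits in the Analysis section, which anchors the comparison to the end of treatment. The waitlist arm has no treatment in the controlled period, so that anchor does not by itself define a date for it.

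**Working it through.** **Inputs**

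- Length of the course: 24 sessions at 3 per week (Acupuncture intervention; Table 1).
- Lag in the disputed sentence: 8 weeks after the final treatment (Outcome measures).
- Waitlist course: begins after the 8-week wait and lasts 8 weeks (Abstract; Randomization and allocation).
- Endpoint elsewhere: week 8 (Abstract; Primary outcome), with waitlist evaluations done inside the first 8 weeks after randomisation (Table 1).

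**Calendar arithmetic, in weeks from randomisation, taking treatment to start at about randomisation**

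1. Final treatment in the acupuncture arm: 24 / 3 = 8, so about week 8.
2. Literal date of the last assessment in that arm: 8 + 8 = about week 16.
3. Waitlist course: from week 8 to 8 + 8 = week 16.
4. Gap between the literal date and the week-8 endpoint: 16 − 8 = 8 weeks.

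**What the literal sentence could mean for the waitlist arm**

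| Reading | Acupuncture arm | Waitlist arm | Consequence |
|---|---|---|---|
| Both arms on the acupuncture arm's calendar | week 16 | week 16 | waitlist arm already offered its course |
| Each arm after its own final session | week 16 | 16 + 8 = week 24 | waitlist arm already offered its course, and times differ |
| Waitlist arm held to Table 1 | week 16 | week 8 | times from randomisation differ by 8 weeks |
| Slip; week 8 intended | week 8 | week 8 | agrees with the other sections |

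Only the last row compares acupuncture with no acupuncture at a common time from randomisation.

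**Does the sample size depend on this?** The inputs in the Sample size section are a difference of 14.5, SD 14.5, one-tailed alpha 0.05, power 0.80, allocation 2:1 and 20% drop-out.

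- Waitlist arm: n = (1 + 1/2) × (1.645 + 0.842)² × (14.5 / 14.5)² = 1.5 × 6.185 = 9.28, rounded up to 10. The acupuncture arm is then 20. An exact t calculation gives the same numbers, with power 0.809.
- Drop-out: 10 / 0.8 = 12.5, rounded up to 13. At 2:1 the acupuncture arm is 26, and the total is 39.

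The stated 26 + 13 = 39 is reproduced. The date of the last assessment does not enter this calculation.

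**The case against.** The strongest reply is that the intended time is not seriously in doubt. The Abstract, the Primary outcome section and both relevant rows of Table 1 point to week 8, and the Analysis section's end of treatment falls at about the same time. The Design section describes only a screening period and an 8-week treatment period, with no later follow-up. Outcome measures lists the same sequence as the Primary outcome section (first visit, five weeks, eight weeks). With one comma, its last item becomes an assessment at eight weeks, made after the final session. All of this stands, and it makes a wording slip the likely explanation.

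A reader might infer that the trial planned a week-16 comparison of two treated arms, and that the expected contrast would fall from 14.5 points towards zero. The document does not support that. No section schedules a waitlist measurement at week 16, and Table 1 excludes one as part of the controlled evaluations. The fall towards zero would need both arms to be measured then, and nothing in the document gives a basis for its size.

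The reply does not remove the contradiction. The sentence is operative text in the section that sets out when outcomes are measured, and it has to be corrected rather than inferred away. Figure 1, the chronological flow chart, is not reproduced in the text available, so it cannot be used to settle the matter or be called wrong.

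**Conclusion.** The point holds as an internal contradiction about the timing of the primary endpoint and of the secondary measures taken at the same visit. Outcome measures is wrong as printed: it differs by 8 weeks from the Abstract and the Primary outcome section, and it conflicts with the control definition in Table 1. Followed literally, there would be no week-8 assessment, and the late one would not give a comparison with an untreated arm at a common time.

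The conclusion assumes that treatment starts at about randomisation and that the 24 sessions run on schedule. Modest delays would move the dates but not remove the conflict. It is not evidence that the trial intended a later comparison. The sample size of 39 is unaffected, and no loss of effect or power should be attached to this point.

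**What to change.** In Outcome measures, reconcile the timing with the Abstract, the Primary outcome section and Table 1. Suggested wording: *at the first visit, and at 5 and 8 weeks after randomisation in both groups, the week-8 assessment being completed before any waitlist participant starts acupuncture*. The last clause only restates what Table 1 already requires of the control group.

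In Analysis, replace the end-of-treatment anchor with week 8 after randomisation, so that the comparison has one date that applies to both arms.

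The cost is one sentence and one phrase, with a check that Figure 1 and the visit schedule used at the site show the same dates. No recalculation is needed.

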#### Data and safety monitoring

Regular monitoring will be conducted at the investigational site for quality control. Additionally, investigators convene to discuss practical issues that may be encountered, such as adjusting recruitment capacity, dealing with serious adverse events, revising the protocol, and other important issues that may be raised by investigators and participants. The assessment of safety will primarily be based on the frequency of adverse events, which will include all serious adverse events. Information regarding adverse events will be summarized by presenting the number and percentage of the participants who experienced them. The data will also be categorized according to the affected body region. All of the other information collected (e.g., severity or relation to acupuncture treatments) will be listed appropriately.

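### The adverse-event recording sentence is limited to events caused by acupuncture, which is inconsistent with the planned comparison of event percentages between the acupuncture and waitlist groups

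*Protocol article*

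**What the plan says.** Safety is part of the main aim (Objective): "The primary objective of this study is to investigate the efficacy and safety of acupuncture in patients with sequelae of Bell's palsy".

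Four statements in the protocol article bear on how adverse events are handled:

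- **Recording** (Outcome measures): "Any adverse events as a result of acupuncture will be monitored and recorded". No other sentence says what is to be monitored and recorded as an adverse event.
- **Reporting** (Analysis): "All adverse events reported during the study will be included in the clinical report, and the prevalence of adverse events will then be calculated".
- **Testing** (Analysis): "The percentage of subjects with adverse events in each group will be calculated and compared using the chi-squared test or Fisher's exact test".
- **Assessment and listing** (Data and safety monitoring): "The assessment of safety will primarily be based on the frequency of adverse events, which will include all serious adverse events", and later "All of the other information collected (e.g., severity or relation to acupuncture treatments) will be listed appropriately".

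On the comparator, Table 1 under Acupuncture intervention says (quotation cut one word before its end): "The control group forms a waitlist and completes the evaluations during the first 8 weeks after randomization before receiving the same treatment as the acupuncture". The waitlist group therefore receives no acupuncture between randomization and the week-8 evaluation, and is treated after that.

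**The concern.** The recording sentence makes causation by acupuncture part of the description of a recordable event. A group that has had no acupuncture cannot meet that description. Yet the Analysis section compares the two groups on the percentage with events. That comparison is informative only if events are sought in the same way in both groups whatever their cause. Listing relation to acupuncture as a collected item also presupposes that unrelated events are on file. Otherwise the item could take only one value.

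For safety, the waitlist group's use is to show how often events occur without needling. If the recording sentence is followed literally, that background rate is lost. The acupuncture-group count then depends on how many events someone judged to be caused by the needles. The result could be a spurious excess or an empty table, with no difference in true harm. Analysis cannot repair this afterwards, because events that were never recorded cannot be recovered.

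**Working it through.** **1. The statements side by side.**

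| Section | What it covers | Limited by cause? | Applies to both groups? |
|---|---|---|---|
| Outcome measures | monitoring and recording | yes, to events resulting from acupuncture | not possible for the waitlist in weeks 0 to 8 |
| Analysis | reporting and between-group test | no | yes |
| Data and safety monitoring | summary; listing of relation | no; relation is a separate attribute | not stated |

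The first row cannot be the collection rule if the other two are to work as described.

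**2. Denominators.** The Sample size section gives 26 and 13, and these reproduce. With difference 14.5, SD 14.5, one-sided alpha 0.05, power 0.80 and 2:1 allocation, the waitlist number is (1.645 + 0.842)² × (1 + 1/2) × (14.5/14.5)² = 6.18 × 1.5 = 9.3, so 10, with 20 on acupuncture. Allowing 20% drop-out, 10/0.8 = 12.5, so 13. Keeping 2:1 gives 26.

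**3. Where the test crosses 0.05 if the waitlist count is 0/13.** Two-sided Fisher exact p for k/26 versus 0/13:

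| k | 6 | 7 | 8 | 9 |
|---|---|---|---|---|
| p | 0.081 | 0.073 | 0.035 | 0.018 |

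Check for k = 8. The observed table has probability C(26,8)/C(39,8) = 1,562,275/61,523,748 = 0.0254. The tables in the other direction that are no more probable, with 6, 7 or 8 of the 8 events on the waitlist, add 0.0091 + 0.0007 + 0.00002. The total is 0.035. The chi-squared test without continuity correction, which the plan also allows, crosses one event sooner (7/26, p = 0.039).

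**4. Chance of a significant result with no true harm.** The documents give no event rate, so r, the proportion of participants with an event of any cause over 8 weeks, is an assumption and is varied.

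- *Literal recording, every acupuncture-group event attributed:* the waitlist is 0/13, and p ≤ 0.05 requires at least 8 of 26. The chance is P(X ≥ 8) with X ~ Binomial(26, r).
- *All-cause recording in both groups:* X ~ Binomial(26, r) and Y ~ Binomial(13, r), summing the probabilities of all tables with Fisher p ≤ 0.05.

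| r | Literal recording, full attribution | All-cause recording, both groups |
|---|---|---|
| 10% | 0.003 | 0.018 |
| 20% | 0.13 | 0.027 |
| 30% | 0.54 | 0.030 |
| 40% | 0.88 | 0.033 |

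**5. Partial attribution.** What enters the first column is the recorded rate, that is, r times the share of affected participants whose event is attributed. A background rate of 40% with half attributed gives 40% × 0.5 = 20%, hence about 0.13. With nothing attributed, the table is 0/26 versus 0/13 and there is nothing to test.

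**The case against.** The strongest reply is that the article nowhere sets an exclusive rule. A reader might infer that events are recorded only if attributed to acupuncture, and that the waitlist count is zero by definition. The text does not support that as fact. The sentence says that events resulting from acupuncture are recorded; it does not say that others are not. The Analysis section reports all events by group, and Data and safety monitoring includes all serious events and keeps relation as a separate item. Together these suggest that all-cause recording was intended. Any zero would also apply only until the waitlist group starts its own treatment after week 8.

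Two further inferences should not be drawn:

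- **That an unblinded investigator decides attribution.** No section says who records or attributes events. Randomization and allocation says only that the person giving acupuncture cannot be blinded.
- **That worsening of facial symptoms would go unseen.** FDI, House-Brackmann grade, lip mobility and stiffness are assessed at scheduled visits in both groups and would show it.

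It is also fair that the larger probabilities need a high background rate together with full attribution. At 10% there is practically no false excess.

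What remains is the inconsistency. The sections that point to all-cause recording govern reporting, testing and listing, and they act on what has been collected. A site that follows the one sentence on recording could leave waitlist events unrecorded and still comply with the text. Nor is this a detail left to a fuller document: the article states a recording rule, and that rule does not fit its own planned test.

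**Conclusion.** The point holds as an internal inconsistency, with medium confidence. The Outcome measures wording cannot be squared with the between-group comparison in Analysis or with the separate relation item in Data and safety monitoring. The consequence is conditional: if that wording governs collection, the waitlist group supplies no background rate in weeks 0 to 8 and the test measures attribution.

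Under the further assumptions of no true harm and full attribution, the false-positive chance runs from 0.003 at a 10% background rate to 0.88 at 40%, against 0.018 to 0.033 with equal all-cause recording. With no attribution the distortion goes the other way and no events are seen. The rates are assumptions, so the table shows how far the result could be driven by the recording rule and does not forecast what this trial will find. The correction should be made, because safety is in the primary objective and unrecorded events cannot be restored later.

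**What to change.** Reword the sentence in Outcome measures, for example:

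> All adverse events, whatever their cause, will be recorded in the same way in both groups from randomization to the end of each participant's participation, including the period when the waitlist group is treated. Relation to acupuncture will be recorded as a separate attribute.

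In Analysis, state that the between-group comparison uses all-cause events from randomization to the week-8 evaluation. The present phrase about events during the study leaves that window open. List separately the events judged related to acupuncture and the waitlist group's events after week 8. Recording should not stop at week 8, because up to 13 waitlist participants begin acupuncture then.

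The cost is a sentence or two in the protocol and matching wording on the case report form. Some unrelated minor events will also be recorded. No extra visits or participants are needed.
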